### Effects of reduced consumption

Using another regression, we will further analyze questionnaire data collected at the beginning, during the intervention, as well as during the post-questionnaire, to investigate, whether reduced consumption affects life-satisfaction. We expect it to increase within both experimental groups, negatively correlating with excessive consumption.

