## Objectives

The project will test whether user-generated content promoting either self-transcendence or self-enhancement values and goals could be effective in reducing excessive consumption, as well as increasing well-being. The effectiveness of the interventions will be tested by measuring their effects on life-satisfaction, intent to adopt voluntary simplicity, and purchasing intent and behavior. The project's main research questions are:
Could user-generated content promoting voluntary simplicity reduce excessive consumption?Are self-enhancement goals as effective in promoting sustainable behavior as self-transcendence goals, in user-generated Minimalism content?

We are also interested in whether exposure to user-generated content promoting voluntary simplicity affects one's well-being. Finally, the relationship between one's intent to reduce consumption and one's consumption behavior might generate meaningful insights.

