## Procedure

At baseline, all participants will download a free mobile application. Participants will complete an intake survey on Qualtrics, through a link in the mobile application. Following intake, participants will be randomly allocated to one of the three experimental conditions, and complete a battery of questionnaires measuring dependent and independent variables (see t0 in Figure 1). After baseline measurements, the intervention will commence. In the two intervention conditions, participants will watch one video daily for 6 days. Both intervention and control condition participants will complete a daily mood measurement (see t1 through t6 in Figure 1). On the last day of the intervention, participants will complete questionnaires measuring the dependent and independent variables a second time (see t7 in Figure 1). One month after intervention completion, the dependent variables will be measured again (see t_end_ in Figure 1).

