After the intervention is completed, including a one-month follow-up, the research team will conduct initial analysis on the effectiveness of the employed interventions. Specifically, conducted analysis will test whether either one or two of the employed interventions prove to be beneficial in reducing excessive consumption and increasing well-being, in comparison to the control condition. If one or both interventions prove to be effective, they will be offered to participants who did not experience them while participating in the study. Thus, all participants will be afforded the opportunity to take part in an effective intervention for consumption reduction, should the research team identify one. Participants will also receive debriefing of the study and will be exposed to all three conditions employed in the study design.

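### The one life-satisfaction model written out treats achieved consumption reduction, which is not randomised, as the cause, and so does not deliver the comparison with control promised elsewhere

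*Protocol article*

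**What the plan says.** *Objectives* makes life satisfaction an outcome of the interventions: "The effectiveness of the interventions will be tested by measuring their effects on life-satisfaction, intent to adopt voluntary simplicity, and purchasing intent and behavior". The same section adds an interest in whether "exposure to user-generated content promoting voluntary simplicity affects one's well-being". *Ethics process* describes an initial effectiveness analysis after the one-month follow-up. It is to look at benefit in reducing consumption and in "increasing well-being, in comparison to the control condition", and its result decides whether an intervention is offered to participants who did not receive it.

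Under *Proposed analysis*, life satisfaction appears only in *Effects of reduced consumption*. There a further regression is to be used "to investigate, whether reduced consumption affects life-satisfaction", and the expectation is: "We expect it to increase within both experimental groups, negatively correlating with excessive consumption". That subsection does not list the predictors. It names neither condition nor the control group.

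**The concern.** The objective concerns a randomised exposure; the model described concerns a behaviour that participants choose after randomisation. Randomisation protects the first comparison and does not protect the second. Stress, a change in income or a shift in mood during the week could alter both buying and satisfaction. Stress that raises buying and lowers satisfaction would by itself produce the negative correlation the authors expect.

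The expected rise inside the experimental groups is no safeguard. *Participant criteria* admits people who want to reduce their consumption and find it hard, and *Consumption reduction—behavior* itself expects change over time in every condition, control included. Without the control contrast, a rise in the video groups cannot be credited to the videos.

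If the subsection were followed as written, an association would be reported with a causal verb, on an outcome that the article counts among its tests of effectiveness.

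**Working it through.** **1. How each outcome is modelled in the article**

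| Subsection of *Proposed analysis* | Explanatory factor named | Control contrast or expectation stated |
|---|---|---|
| *Consumption reduction—behavior* | Condition, with baseline as covariate | Yes, stronger reduction than in control |
| *Consumption reduction-intent* | The interventions, in a similar regression | Time-by-condition interaction |
| *Changes in values and motivations* | Exposure to the stimuli | Yes, expectation given for each arm, control included |
| *Effects of reduced consumption* (life satisfaction) | Reduced consumption | None |

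The article names condition or the interventions where it means them. The life-satisfaction subsection is the only one that puts a post-randomisation behaviour in that place.

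**2. Size of the confounding risk (illustration)**

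The plan gives no figure for this analysis, so there is none to reproduce. The only input from the article is the sample: *Sample size* recruits 250 with 20% dropout assumed, so 250 × 0.80 = 200 completers. The rest is assumed: no causal effect of consumption on satisfaction, one common cause correlated *a* with each variable, no adjustment, two-sided 5% test.

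- Induced correlation: r = a²
- Rejection probability ≈ Φ(atanh(r) × √(N − 3) − 1.96), with √197 = 14.04; the opposite tail is negligible

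| a | r = a² | atanh(r) × 14.04 | minus 1.96 | Rejection |
|---|---|---|---|---|
| 0.3 | 0.09 | 1.27 | −0.69 | 24% |
| 0.4 | 0.16 | 2.27 | 0.31 | 62% |
| 0.5 | 0.25 | 3.58 | 1.62 | 95% |

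**3. Cross-check by simulation**

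Assumptions: 66 per arm (198 in three equal arms; the allocation ratio is not stated), videos reduce consumption by 0.4 SD, neither condition nor consumption affects satisfaction, a common cause leaves residual correlation r, 2,000 runs.

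| r | Rejects, regression on consumption reduction | Rejects, regression on condition |
|---|---|---|
| 0 | 5% | 5% |
| 0.1 | 28% | 5% |
| 0.2 | 81% | 5% |
| 0.3 | 99% | 4% |

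The regression on condition keeps its nominal level whatever the confounding. The regression on consumption does not.

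**4. Can the planned sample carry the condition model?**

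For one intervention arm against control, with 66 per arm, 80% power, two-sided 5% and baseline adjustment, the detectable difference in SD units is (1.96 + 0.84) × √(1 − ρ²) × √(2/66). For an assumed baseline–post correlation ρ of 0.5, 0.7 and 0.84 this is 0.422, 0.348 and 0.265 SD. For both interventions pooled against control (132 v 66), replace √(2/66) by √(1/66 + 1/132), which gives 0.366, 0.302 and 0.229 SD. The model can be run on the planned sample with no change to N.

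**The case against.** The strongest reply is that the randomised comparison is already promised. *Ethics process* commits to testing well-being against control. *Design* says the two interventions will be compared with control and makes before–after differences the dependent variables. *Post-intervention questionnaire* defines effectiveness as that difference adjusted for covariates, with every intake scale repeated. A reader might infer that the plan has no test of the interventions' effect on well-being, or that consumption has replaced condition as predictor. The documents support neither inference: the commitment is there, and the life-satisfaction subsection neither lists its predictors nor excludes condition. The authors also speak of reductions within the experimental groups when discussing consumption, where a control contrast clearly is planned.

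A reader might also see a contradiction in that subsection's use of data from during the intervention, since only mood is scheduled then ("Both intervention and control condition participants will complete a daily mood measurement"). That wording is loose but not inconsistent: the daily mood scores are questionnaire data and could enter the model.

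It is fair, too, that the rejection rates follow from chosen correlations and an unadjusted model. Pre/post differences with covariates would remove some stable shared causes, though not those that change during the study. The link between consumption and satisfaction is also a legitimate further question.

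What remains is a mismatch. This is more than model detail that an article may leave to a fuller document: for this outcome the article does describe a model, and the model answers a different question from the one set in *Objectives* and *Ethics process*.

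**Conclusion.** The point holds as a mismatch between objective and described analysis. *Effects of reduced consumption* asks a causal question about a non-randomised variable and states no contrast with control, while *Objectives* and *Ethics process* promise the effect of the randomised interventions. The promise of a comparison with control stands, so the test is not absent from the plan; the model described simply does not deliver it.

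The size of the possible error is not known from the documents. Under the assumed correlations of 0.3 to 0.5 it runs from 24% to 95% false rejection at N = 200, unadjusted. That the regression on consumption is open to confounding, and the comparison by condition is not, does not depend on those values; the rates do.

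**What to change.** In *Effects of reduced consumption*:

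- Make the test of the interventions' effect an analysis of life satisfaction at t7 and at t_end with the model already given in *Consumption reduction—behavior*: contrast-coded condition versus control, with baseline life satisfaction as covariate.
- Keep the regression of life satisfaction on consumption reduction as a secondary analysis, with condition and the baselines of both variables in the model. Report it as an association and drop the causal verb.

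Cost: one extra model on data already scheduled for collection, plus the wording. No new measurement and no change to the sample size.

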### Changes in values and motivations

Using a repeated-measures ANOVA, with *post-hoc* contrasts, we will also compare in-take measurements of participants' values and motivations to the two post-intervention measurements. Thus, we will test whether exposure to the intervention stimuli affected consumer values and motivations directly. We expect participants in the self-transcendence condition to show an increase in biospheric values and motivations at t7, while participants in the self-enhancement condition will show an increase in egoistic values and egoistic and hedonic motivations at t7. Control condition participants are not expected to show a significant change in either values or motivations during the intervention. This measurement will serve as a manipulation-check. We will also explore whether the manipulation persists at t_end_, one month following the intervention.

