### Participant outreach

#### Sample size

Two hundred and fifty English-speaking subjects will be recruited for this study globally, via online methods. The number of participants needed is based on an a priori power analysis using G^*^Power software (*F*-test, ANOVA: Repeated measures, within-between-interaction; 1− β = .80, α = .05, Cohen's f = .10), which revealed that the study would require a total sample size of *N* = 198 (Faul et al., 2007). An additional 52 participants have been added to this estimated sample size to account for an assumed 20% dropout rate.

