## Proposed analysis

To test the hypotheses, statistical software including Excel, SPSS, and R will be utilized.

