### Consumption reduction—behavior

To examine whether user-generated content will reduce excessive consumption, a multiple regression analysis will be calculated, using condition as an independent variable to predict excessive consumption post-intervention, taking the baseline measurement into account as a covariate, in addition to other controlled variables (e.g., base-line values, demographics). As can be seen in Figure 2, we expect a main effect of point of time for all conditions. In other words, we expect to see consumption behavior decreased post-intervention. Additionally, we expect to see an interaction between point of time and condition, showing a stronger reduction of excessive consumption in the experimental groups following the user-generated content intervention in comparison to the control group.

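### The t7 check on values and motivations is planned as a three-occasion repeated-measures ANOVA, which, run conventionally, drops people who gave t7 data but missed the one-month survey

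*Protocol article*

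**What the plan says.** The section Changes in values and motivations names one method for these outcomes: "Using a repeated-measures ANOVA, with *post-hoc* contrasts, we will also compare in-take measurements of participants' values and motivations to the two post-intervention measurements". The two later measurements are t7 (last day of the intervention) and t_end (one month afterwards), so the analysis covers three occasions.

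The same section ties its predictions to t7. For one arm it says: "We expect participants in the self-transcendence condition to show an increase in biospheric values and motivations at t7". The parallel prediction for the self-enhancement arm is also placed at t7. The purpose is given as "This measurement will serve as a manipulation-check". The one-month point has a lesser role: "We will also explore whether the manipulation persists at t_end_, one month following the intervention".

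On attrition, the Sample size section says: "An additional 52 participants have been added to this estimated sample size to account for an assumed 20% dropout rate". It does not divide that loss into loss before t7 and loss between t7 and one month.

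The Procedure section has dependent and independent variables measured at t7, but mentions only the dependent variables at one month.

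**The concern.** A conventional repeated-measures ANOVA needs a full record on every occasion, and its post-hoc contrasts use the same reduced set. Someone with intake and t7 data who misses the one-month survey therefore contributes nothing to the t7 contrast, although that contrast does not need the missing value.

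Some loss after t7 is plausible from the article itself. The gap from t7 to t_end is a month, against a week for everything before it. The daily reminders stop when the intervention ends. The lottery prize is tied to completing the intervention, and the follow-up is not named.

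Two things are at stake. Usable t7 data are discarded. And if people whom the videos did not move are less likely to return a month later, the check is computed on those who were moved and overstates how well the priming worked. The check supports the comparison of self-transcendence with self-enhancement content, which is the second research question.

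**Working it through.** **1. The plan's own sample size.** Inputs from Sample size: repeated-measures ANOVA, within-between interaction, power 0.80, alpha 0.05, f = 0.10, N = 198. The number of measurements and their correlation are not stated; I assume m = 3, rho = 0.5 and sphericity. There are k = 3 conditions.

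- Noncentrality: lambda = f² × N × m / (1 − rho) = 0.01 × 198 × 3 / 0.5 = 11.88.
- Degrees of freedom: (k − 1)(m − 1) = 4 and (N − k)(m − 1) = 390.
- Power = 0.792, close to the stated 0.80.
- Dropout: 198 / 0.80 = 247.5, so 248, against 250 planned.

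The stated figure is reproduced closely enough under these assumptions.

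**2. How many people the t7 check can lose.** Take 20% as the total loss by one month. Complete on all three occasions: 250 × 0.80 = 200. The number with t7 data but excluded is the number with t7 data minus 200.

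| Lost by t7 (assumed) | With t7 data | Excluded from the t7 check |
|---|---|---|
| 0% | 250 | 50 |
| 5% | 237 | 37 |
| 10% | 225 | 25 |
| 15% | 212 | 12 |
| 20% | 200 | 0 |

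**3. Power on the plan's effect size.** For the intake-to-t7 condition-by-time test (k = 3, m = 2, f = 0.10, rho = 0.5 assumed), lambda = 0.01 × N × 2 / 0.5.

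- N = 200 (complete cases): lambda = 8, power 0.711.
- N = 225: lambda = 9, power 0.765.
- N = 250: lambda = 10, power 0.810.

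**4. Power and bias by simulation.** Inputs: 250 randomised to three arms, 20% lost by one month (from the article); wave correlation 0.7, true t7 shift 0.35 SD against control, and 5%, 10% or 15% lost by t7 (all assumed). The quantity is the self-transcendence versus control difference in intake-to-t7 change, tested at two-sided 0.05.

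- *Random loss.* Complete-case power is about 0.73 to 0.74. With all t7 data it is about 0.80, 0.78 and 0.77 for the three splits, a difference of about 3 to 7 points. Neither estimate is biased.
- *Loss after t7 in the video arms depends on the t7 change* (log-odds 0.5 to 1.0 per SD of change), loss before t7 random:

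| Lost by t7 | Complete-case estimate | All t7 data |
|---|---|---|
| 5% | 0.40 to 0.46 | 0.35 |
| 10% | 0.39 to 0.43 | 0.35 |
| 15% | 0.37 to 0.40 | 0.35 |

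Relative excess: 0.37 / 0.35 = 1.06 at the low end and 0.46 / 0.35 = 1.31 at the high end, so about 6% to 30%.

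- *The same dependence also before t7* (log-odds 1.0). The estimate from all t7 data rises to about 0.39 to 0.46, and the complete-case estimate is about 0.49. Using all t7 data is still better, but it is no longer unbiased.

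**The case against.** The strongest reply is that the exclusion is inferred. The article does not say that incomplete records are dropped or that nothing is imputed, and a condensed article may leave such detail to a fuller plan. That stands as a limit: the absence of a missing-data section is not the point here. The point is that the one method named has an ordinary data requirement that does not suit its stated t7 purpose.

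Second, 200 complete cases meet the planned 198. True, but 198 is reproduced above for a three-occasion interaction; the t7 contrast alone has less power, and meeting a target does nothing about selective loss.

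Third, the size is unknown. This also stands. The split and the loss mechanism are assumptions, and if all loss precedes t7 nothing is lost.

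A reader might also infer that the consumption analysis at t7 necessarily rests on a larger and different set of people, because it works by "using condition as an independent variable to predict excessive consumption post-intervention, taking the baseline measurement into account as a covariate". The documents do not support that. The same part of the article expects a time effect and a time-by-condition interaction, and compares the t7 effect with the one-month effect, without saying whether the waves are analysed separately or jointly. If jointly, that sample too could depend on the one-month survey. Nor may one infer that all available t7 data are free of bias; the last simulation shows otherwise.

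Finally, if values and motivations are not collected at one month, as the Procedure section may imply, the three-occasion analysis cannot be run and this loss does not arise.

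**Conclusion.** The concern holds in a limited form. The named analysis, run conventionally without imputation, makes the t7 manipulation check depend on response to an exploratory survey a month later. The cost is 0 to 50 of 250 people with t7 data. Under the assumed inputs, power falls by about 3 to 7 points, and the estimate is about 6% to 30% too large if loss after t7 in the video arms depends on the t7 change. The upper figure is the extreme case (5% lost by t7, log-odds 1.0). No part of the article establishes the split, the correlation, the effect size or the informative mechanism, so these figures show a range and do not forecast the trial. The direction is firmer: the complete-case set can never hold more t7 data than the available set. This is a manipulation check, and no effectiveness analysis is made conditional on it. The change is worth making because it is easy, but it does not threaten the main results.

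**What to change.** In Changes in values and motivations, state that the t7 contrast uses everyone with t7 data. Either of these would do:

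- a likelihood-based linear mixed model with condition, wave and condition-by-wave, an unstructured covariance over intake, t7 and t_end, and all available measurements; or
- a separate t7 analysis by condition, adjusted for the intake value.

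Keep one-month persistence as a separate contrast. State that bias from informative loss before t7 is not removed by either choice.

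Reconcile the Procedure section with this one on whether values and motivations are measured at one month.

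The analysis change is to wording only and needs no added participants or visits; SPSS and R, both already named, fit either model. If the one-month survey does not at present include the values and motivation items, the persistence question needs them added there or must be dropped.

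### The between-arm test in the manipulation check (values and motivations at t7) would be more precise with intake as a covariate, as the plan already does for consumption

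*Protocol article*

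**What the plan says.** The section Changes in values and motivations sets the method and the data: "Using a repeated-measures ANOVA", with post-hoc contrasts, "we will also compare in-take measurements of participants' values and motivations to the two post-intervention measurements". The stated purpose is causal: "we will test whether exposure to the intervention stimuli affected consumer values and motivations directly". Its expectations are placed at t7: a rise in biospheric scores in the self-transcendence arm, a rise in egoistic and hedonic scores in the self-enhancement arm, and no significant change in the control arm. Persistence at t_end is to be explored. The role is explicit: "This measurement will serve as a manipulation-check".

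The section Consumption reduction—behavior handles the same data structure differently. It predicts the post-intervention value from condition, "taking the baseline measurement into account as a covariate", with contrast-coded condition. The intent analysis uses a similar regression.

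Under Procedure, "participants will be randomly allocated to one of the three experimental conditions". The Sample size section uses "ANOVA: Repeated measures, within-between-interaction" with "1− β = .80, α = .05, Cohen's f = .10", and arrives at N = 198 before allowance for dropout.

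**The concern.** Two analyses of randomised pre-post data in one plan treat the baseline score in two ways. In the ANOVA, the condition-by-time contrast from t0 to t7 compares raw change scores between arms. That subtracts the whole intake score, whatever the correlation, and so carries the intake score's noise into the comparison. A regression with intake as covariate subtracts only the part of the intake score that predicts the t7 score.

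Precision matters here because the result helps readers interpret the consumption results. The second research question compares self-enhancement with self-transcendence goals, and the article expects null results to be informative. A null or equal result on consumption is easier to read if it is clear whether the primes moved values. A less precise check makes it more likely that a real shift in values goes undetected. The intake scores needed for the adjustment are already to be collected from everyone.

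**Working it through.** **Inputs from the protocol article.** Three arms (Procedure); alpha = .05, f = .10, target power .80 and N = 198 (Sample size); occasions t0, t7 and t_end (Procedure; Changes in values and motivations).

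**Assumptions.** The correlation rho between occasions is not stated; I use 0.3 to 0.9. Allocation is taken as equal, 198/3 = 66 per arm. The score variance (sigma²) and rho are taken as the same at each occasion and in each arm.

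**The plan's own figure.** For a within-between interaction with k arms and m occasions, the noncentrality is lambda = f²·N·m/(1−rho), with (k−1)(m−1) and (N−k)(m−1) degrees of freedom.
- k = 3, m = 3, rho = 0.5: the smallest N for 80% power is 202, and power at N = 198 is 0.792.
- k = 3, m = 2, rho = 0.6: the smallest N is 196, or 198 when rounded up to equal arms; power at 198 is 0.805.

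So 198 is reproduced, exactly or nearly, under plausible settings.

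**Variance of the two t7 comparisons.**
- Change score: Var(Y7 − Y0) = sigma² + sigma² − 2·rho·sigma² = 2(1−rho)·sigma².
- Intake as covariate: residual variance = (1−rho²)·sigma².
- Ratio: (1−rho²)/[2(1−rho)] = (1+rho)/2, below 1 for every rho below 1.

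**Power on the two-occasion comparison, f = .10, N = 198.** For the change score, lambda = 0.01·198·2/(1−rho) with 2 and 195 df. For the adjusted model, that lambda is multiplied by 2/(1+rho), with 2 and 194 df. At rho = 0.5, for example, lambda is 3.96/0.5 = 7.92, and 7.92·2/1.5 = 10.56.

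| rho | variance cut | power, change score | power, intake as covariate |
|---|---|---|---|
| 0.3 | 35% | 0.551 | 0.749 |
| 0.5 | 25% | 0.706 | 0.831 |
| 0.6 | 20% | 0.805 | 0.888 |
| 0.7 | 15% | 0.908 | 0.948 |
| 0.8 | 10% | 0.983 | 0.991 |

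At high rho the two columns converge partly because, with f held fixed, power is already near 1. The next calculation removes that ceiling.

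**Same comparison, starting from 80% power.** Take two arms of 66 and set the effect so that the change-score contrast has 80% power. The adjusted contrast then has 93.5% (rho 0.3), 89.9% (0.5), 87.9% (0.6), 86.0% (0.7), 84.0% (0.8) or 82.0% (0.9). Put as sample size, the adjusted model matches the precision of 198 people with 198·(1+rho)/2, rounded up: 149 at rho 0.5, 169 at 0.7 and 179 at 0.8.

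**Against the three-occasion interaction test.** These results come from simulation with 2,000 runs per setting, one arm shifted, and the 4-df interaction set against the adjusted t7 test on 2 df.
- Effect halved by t_end: 0.53 against 0.77 (rho 0.5, shift 0.4 SD); 0.68 against 0.84 (rho 0.8, shift 0.3 SD).
- Effect fully persisting: 0.69 against 0.79 (rho 0.5, shift 0.4 SD); 0.86 against 0.87 (rho 0.8, shift 0.3 SD); 0.79 against 0.78 (rho 0.9, shift 0.2 SD).

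The larger gaps in the first line also reflect an omnibus test that spreads its power over both post-intervention occasions. The planned post-hoc contrasts would recover some of that.

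**The case against.** Repeated-measures ANOVA is a legitimate choice and gives an unbiased comparison under randomisation. It also fits the rest of the plan: the Design section names pre-post differences as the dependent variables, and the sample size was computed for a repeated-measures interaction. So it is not an inconsistency that invalidates anything. All of this stands.

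A reader might infer from the table that the manipulation check is under-powered. The documents do not support that. The lower figures need rho of 0.5 or less on a two-occasion test, whereas the section specifies three occasions and no rho is given. At rho 0.6 the two-occasion test has 0.805, which is on target, and at higher rho it has more.

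A reader might also infer that everyone without a one-month score would be lost from the t7 test. That happens with some ANOVA procedures, but the article names no procedure, and handling of missing data is commonly left to a fuller document. I do not count it.

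Nor does the article make the check a formal gate for the consumption result. The primes are also examined by expert review of the video checklists and by pre-testing.

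Finally, the section predicts changes from intake within each arm, which a t7 regression on condition does not report. That is a fair objection to replacing the ANOVA outright, and the fix allows for it. It does not remove the point, because whether exposure to the stimuli affected values is a between-arm question.

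**Conclusion.** The point holds as one of efficiency. For the between-arm comparison at t7, using intake as a level of time is never more precise than using it as a covariate. On the two-occasion comparison with the plan's f and N, the gain from adjustment is about 13 power points at rho 0.5 (0.706 to 0.831), 4 at 0.7 and 1 at 0.8. From a starting power of 80%, it is about 10, 6 and 4 points. The direction rests on equal variances and a common correlation; the size rests on a rho that the documents do not give. For very stable scales measured a week apart the gain is small, and with a fully persisting effect at rho 0.9 the three-occasion test does as well as an adjusted t7 test. The planned ANOVA is valid, the analysis is secondary, and nothing here touches the main consumption analysis.

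**What to change.** In Changes in values and motivations, make the between-arm test of each value and motivation score a regression of the t7 score on contrast-coded condition, with that score's own intake value as covariate, using everyone with t7 data. Fit a second model of the same form at t_end for the persistence question. Keep the within-arm changes from intake as a descriptive report, so that the predicted pattern in each arm can still be seen.

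The cost is a change of wording in the analysis section. It needs no new data, participants or visits, and the model is the one already planned for consumption.
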